#### 2.5.2. Participant Recruitment and Eligibility Criteria

Participants were recruited for The GRO Project through online platforms (Twitter, Facebook, and Craigslist) and by posting flyers in downtown Louisville. For follow-up visits, all returners were contacted through phone and email information. Participants were excluded for (i) tobacco use within the last 60 days, (ii) uncontrolled cardiovascular disease (CVD) or CVD risk factors such as hypertension, hyperlipidemia, and diabetes mellitus, (iii) ≥stage 3 renal disease, (iv) active cancer, (v) active illicit drug use, (vi) pregnancy, (vii) major trauma within the past 6 months, or (viii) part of a vulnerable population (i.e., children, prisoner, etc.). Additionally, participants were required to be (i) between the ages of 18–75, (ii) able to spend 1 h outdoors in conditions up to a 104 heat index, (iii) capable of walking one mile without limitations, and (iv) have a body mass index lower than 35. Participants were compensated $50 for completion of each in-person exam. The study protocol was approved by the University of Louisville Institutional Review Board (IRB# 23.0437), and written informed consent was obtained prior to testing.

### 2.6. Study Visit Protocol

#### 2.6.1. Study Characteristics

In Wave 1, we recruited 40 participants, of whom 25 returned for Wave 2. We further supplemented Wave 2 with 25 new participants (Figure 3C). We anticipate collecting another ~60 participants in Wave 3. Demographic characteristics of participants in Waves 1 and 2 are presented in Table 3. Participants from Waves 1 and 2 will be contacted for post-intervention follow-up visits during future waves.

#### 2.6.2. Randomization and Visit Procedures

Trained personnel conducted all study visits. At baseline, we randomized participants to one of two groups, which determined the sequence of conditions: either the microforest (test site), followed by a nearby parking lot (control site), or vice versa (Figure 3A). Testing lasted 40 min for each location, conducted either at 8:30 AM or 10:15 AM to minimize circadian variation. The second visit was temporally matched with the start time of the first visit. Each visit began with electronic questionnaires, application of wearable biomonitors, and baseline collection of biomonitor data and biospecimen sampling. Following baseline measures, we guided participants outside to spend 20 min resting in a chair and 20 min walking at a self-selected leisurely pace. Following the 40 min session, participants returned indoors to complete post-exposure questionnaires and provide additional urine and saliva samples (Figure 3B). The study visits were temporarily separated and conducted on distinct days. Acute thermal and cardiovascular responses (e.g., HRV, blood pressure, and cortisol) are expected to return to baseline within hours following exposure.

#### 2.6.3. Questionnaires and Psychosocial Measures

We administered electronic questionnaires prior to the first visit that included demographic characteristics, medical history, perceived stress, perceptions of nature, and behavioral habits (Supplementary Table S1). On the day of the in-person exam, participants were instructed to refrain from eating or drinking 30 min prior to the start of each visit. Height and weight were measured upon arrival. Each visit began with the State-Trait Anxiety Inventory (STAI) [58] to assess current anxiety levels. For 2024, the Subjective Units of Distress Scale (SUDS) was added to measure distress. For 2025, the Brief State Rumination Inventory (BSRI) [59] was also added to assess rumination.

#### 2.6.4. Physiological and Cardiovascular Measurements

Following questionnaires, we began physiological monitoring, which included ambulatory blood pressure, heart rate (HR), heart rate variability (HRV), axillary temperature, and biospecimen measures. In Wave 1 (2023), blood pressure was recorded every 5 min using a Mobil-O-Graph device (IEM GmbH; Aachen, Germany); in Wave 2 (2024), we switched to an iHealth Neo ambulatory cuff (Vivalink; Campbell, CA, USA) to improve data quality and link backend data temporally under the same Vivalink device network. Both blood pressure devices are FDA-cleared and validated for ambulatory blood pressure measurement, and calibration checks were performed prior to deployment. For Waves 1 and 2, we measured HR and HRV continuously with the multi-vital electrocardiogram (ECG) patch (Vivalink; Campbell, CA, USA) at 128 Hz. We also added axillary temperature in Wave 2, measured by an FDA-approved, clinical-grade patch that records in 12 s intervals (Vivalink; Campbell, CA, USA).

#### 2.6.5. Biospecimen Collection

Spot urine samples were collected to assess chemical exposure and salivary samples to measure cortisol. Spot urine samples were collected at baseline and 30 min post-exposure to allow for metabolism of biotic and abiotic chemicals. Saliva samples (~1 mL) were taken at four timepoints in 25 min intervals, including baseline, seated outdoors, walking outdoors, and post-exposure, to establish a cortisol curve. A detailed summary of all exam procedures is provided in Table 4. Throughout the visits, participants carried an AirBeam personal air quality monitor (HabitatMap), which continuously measured particulate matter (PM_1_, PM_2.5_, and PM_10_), humidity, and temperature. Additional environmental monitoring included a micro-aethalometer for black carbon (BC), a portable gas monitor for NO_2_, a noise monitor, and a HOBO data logger with GPS to track ambient temperature and relative humidity.

### 2.7. Integrated Ecological, Environmental, and Human Health Conceptual Framework

This urban microforest intervention modifies local environmental conditions, which changes individuals’ exposure to heat and pollutants during walking. These exposure differences are hypothesized to influence human health (cardiovascular and stress-related) responses measured in the randomized crossover study. As shown in Figure 4, the integrated framework links site-level ecology and microclimate to personal environmental exposure and, ultimately, to human health response.

### 2.8. Greening Intervention: The [name] Microforest

#### 2.8.1. Site Preparation and Infrastructure

The intervention began after completion of the first round of baseline testing in Summer 2023. Initial site modifications included the removal of the existing central walkway and the installation of a semi-circular retaining wall, along with a new perimeter walking path (Figure 5). The retaining wall is three feet tall and spans 188 feet, and the wall’s thickness varies from one to two feet to support the weight of the new soil. Benches and lighting were added, and the retaining wall was backfilled with approximately 700 tons of Nugent soil to create a three-foot raised area sloping southward. In addition, metal signage and fins were installed on the south side of the retaining wall to complete the circle, with the signage being 66 inches in height and four inches thick, and the metal fins being 60 inches in height and one inch thick (Supplemental Figure S2). This middle well zone was planted with grass, and mulch was applied along the park’s edges prior to the wave 2 physiological assessment in Summer 2024.

#### 2.8.2. Planting Design and Species Composition:

The primary phase of greening occurred in Winter 2024 and extended into the following months. A total of 119 trees representing 31 species were planted (Supplementary Table S2), comprising a mix of deciduous (primarily Anacardiaceae, Fabaceae, and Fagaceae families) and evergreen species (mainly Pinaceae). This combination was selected to maximize cooling benefits in a temperate climate and enhance year-round canopy cover. In addition, 242 shrubs and hundreds of herbaceous groundcover plants were installed across the site (Supplementary Table S3). Plant material was sourced from nurseries in multiple states and transported directly to Louisville to minimize storage stress prior to planting.

Trees were planted in close spacing (1–1.5 m apart) to accelerate canopy closure. Shrubs were positioned between rows to form a layered understory, while herbaceous species and groundcovers filled interstitial spaces. This stratified planting scheme was designed to mimic natural forest succession, increase soil infiltration, suppress weeds, and promote early biodiversity. Collectively, these dense plantings are expected to enhance evapotranspirative cooling, mitigate urban heat, and improve ecosystem resilience (Figure 6A,B). Progress of installation is shown in Figure S3.

### 2.9. Data Analysis

#### 2.9.1. Statistical Analysis Overview

Descriptive statistics will be calculated for all outcomes, demographic variables, and environmental exposures. Continuous variables will be assessed for normality; skewed outcomes will be transformed as appropriate. Primary analyses will compare personal exposure to temperature, humidity, and particulate matter (PM) between the two walking sites (microforest vs. parking lot) using both personal monitors and fixed/mobile monitoring data.

#### 2.9.2. Primary Analyses

The primary outcomes are changes in HRV and blood pressure. Linear mixed-effects models will be used to evaluate associations between temperature and these outcomes, accounting for the crossover, repeated-measures design. Participants will be modeled as random effects, with treatment (microforest vs. parking lot) and sequence (site order) as fixed effects. An interaction term between temperature and treatment will test whether walking in the microforest modifies temperature–health associations. Linearity of associations will be assessed using splines. Given the change in blood pressure-measuring devices between Waves 1 and 2, the study wave will be included as a covariate in statistical modeling to account for any systemic device-related differences, and sensitivity analyses will assess whether results differ by device. Carryover effects due to insufficient washout in the carryover design will also be evaluated by including sequence and period effects in the mixed-effects models.

Potential confounders will be identified using directed acyclic graphs (DAGs). Models will adjust for age, sex, race, BMI, education, particulate matter levels, and hypertension status. Effect modification by sex and PM concentrations (PM_1_, PM_2.5_, and PM_10_) will also be tested. Sensitivity analyses will examine the influence of medication use and prior smoking history.

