#### 2.9.3. Correlation Structure

A covariance structure will be incorporated to account for within-subject correlation across repeated measures during each study day. Changes in health endpoints will be expressed as percent change with 95% confidence intervals.

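### Sequence and period terms cannot isolate carryover in this two-visit crossover, and the pre-exposure HRV and blood pressure taken at each visit are not among the model covariates

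*Protocol article*

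**What the plan says.** Section 2.6.2 describes two sequences of two visits: "either the microforest (test site), followed by a nearby parking lot (control site), or vice versa". A pre-exposure baseline is taken every time: "Each visit began with electronic questionnaires, application of wearable biomonitors, and baseline collection of biomonitor data and biospecimen sampling". The visits fall on distinct days, and acute responses are expected to resolve within hours.

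Section 2.9.2 defines the endpoints and the model: "The primary outcomes are changes in HRV and blood pressure", and "Participants will be modeled as random effects, with treatment (microforest vs. parking lot) and sequence (site order) as fixed effects". The covariates are fixed by name: "Models will adjust for age, sex, race, BMI, education, particulate matter levels, and hypertension status". For carryover it says: "Carryover effects due to insufficient washout in the carryover design will also be evaluated by including sequence and period effects in the mixed-effects models". Section 2.9.3 adds: "Changes in health endpoints will be expressed as percent change with 95% confidence intervals". The reference point of the change is not stated in either section. No check of the second-visit baseline is described.

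**The concern.** There are two separate issues.

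**Carryover.** The article commits to a specific method. In a design with two sequences and two periods, that method cannot separate carryover from other explanations. A non-significant sequence or period term could then be reported as support for adequate washout when it is not evidence of that.

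**Precision.** Apart from particulate matter, the named covariates describe the participant rather than the visit, so they do little for a within-person comparison of two sites. The same-visit pre-exposure HRV or blood pressure is the measured covariate most likely to sharpen that comparison, and it is not listed. A change score would use it, but with its coefficient fixed at 1 instead of estimated.

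**Working it through.** **The plan's own figure.** Section 2.10 gives SDNN of 31.0 and 22.6 (difference 8.4), SD 6.7 and α = 0.025, and claims power above 90% at n = 50 and above 85% at n = 40. The between-visit correlation ρ and the sidedness are not given; I assume a two-sided test. For a paired t-test the SD of the difference is 6.7 × √(2(1−ρ)). With ρ = 0 this is 9.48, and power is 99.99% at n = 50 and 99.9% at n = 40. The HRV claim is met. Blood pressure has no inputs, so its figure cannot be reproduced.

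**Carryover: aliasing.** Take each wave as one two-visit crossover. Code the four cells by sequence (1 = microforest first), period (1 = second visit) and treatment (1 = microforest). Let the microforest leave a carryover λ, which then appears only in the microforest-first group at visit 2. The same four means are produced exactly, with no carryover at all, by sequence = ½λ, period = ½λ and treatment = −½λ:

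| Cell | Sequence | Period | Treatment | Sum |
|---|---|---|---|---|
| Microforest first, visit 1 | ½λ | 0 | −½λ | 0 |
| Microforest first, visit 2 | ½λ | ½λ | 0 | λ |
| Parking lot first, visit 1 | 0 | 0 | 0 | 0 |
| Parking lot first, visit 2 | 0 | ½λ | −½λ | 0 |

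The design matrix has rank 4 before a carryover column is added and rank 4 after. Carryover therefore biases the treatment estimate by half its size and has no coefficient of its own.

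**Carryover: the sequence test is weak.** It compares participant totals between the two groups. On SDNN levels with SD 6.7 and n = 50 split equally, its standard error is 6.7 × √(2(1+ρ) × 4/50). The treatment standard error is 6.7 × √(2(1−ρ)/50).

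| Assumed ρ | SE, carryover via sequence | SE, treatment | Carryover detectable with 80% power at 0.05 (2.80 × SE) |
|---|---|---|---|
| 0.3 | 3.06 | 1.12 | 8.56 |
| 0.5 | 3.28 | 0.95 | 9.20 |
| 0.7 | 3.49 | 0.73 | 9.79 |

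Carryover would have to be at least as large as the whole assumed treatment effect of 8.4 to be found reliably, and a positive result still could not be attributed to it.

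**Carryover: change scores.** If θ is the carryover in the visit-2 baseline and λ that in the visit-2 response, the change contains λ − θ. When the two are equal nothing remains, and the sequence term is blind to it.

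**Carryover: what the baselines add.** The visit-1 baseline shows the group difference before any exposure. With baselines there are eight cell means, and a model with sequence, time, treatment, θ and λ has rank 8 of 8. So θ can be separated from a stable group difference. Separating λ as well still requires assuming no treatment-by-period interaction.

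**Precision.** Let r_w be the baseline-to-exposure correlation within a visit and r_b the correlation between visits, with equal variances σ². Neither is given. For the within-person differences between visits:

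- variance of each difference: V = 2σ²(1−r_b)
- their correlation: b = (r_w−r_b)/(1−r_b)
- change score: 2V(1−b)
- baseline-adjusted: V(1−b²)
- ratio: 2/(1+b)

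For b = 0.7 the ratio is 2/1.7 = 1.18, and for b = 0.3 it is 2/1.3 = 1.54. The standard error is then 8% to 24% larger (√1.18, √1.54). Fifty participants carry the information of 50 × 0.85 = 42.5 down to 50 × 0.65 = 32.5. Examples: r_w = 0.8 with r_b = 0.5 gives b = 0.6 and 1.25; r_w = 0.7 with r_b = 0.5 gives b = 0.4 and 1.43.

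**Effect on stated power.** If 6.7 is the SD of a single level and r_w = 0.5, the change-score contrast has SD 6.7 × √(4 × 0.5) = 9.48. Power is again 99.99% and 99.9%.

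**The case against.** The best defence has five parts.

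- **The change is not defined.** Section 2.10 powers the trial on site levels, and a percent change may be a back-transformed model coefficient. This stands: the precision point is conditional on reading the change as change from the visit baseline.
- **The design protects against carryover.** Visits are on separate days and recovery is expected within hours of a 40-minute session. This stands as a reason to expect little carryover. It does not make the stated evaluation informative.
- **The article never says a null term proves washout, nor that the model will be chosen on it.** True, but it does call these terms an evaluation of carryover from insufficient washout, which invites that use.
- **Details belong in the analysis plan, and confounders will be identified with causal graphs.** An unseen plan may add a baseline term. However, the article itself names the covariates and the carryover method, and that method cannot work in this design.
- **Baseline adjustment has its own weakness.** If carryover shifted baseline and response equally, a change score would cancel it, while adjustment would leave a treatment bias of ½(1−b) times the shift. For an illustrative shift of 4.2 and b = 0.5 this is ½ × 0.5 × 4.2 = 1.05. This stands as a small trade-off.

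A reader might also infer more than the article supports:

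- **That the period term is useless.** It is not; it absorbs part of any carryover and is needed for ordinary period effects.
- **That percent changes will be analysed despite skewness.** Section 2.9.1 provides for transforming skewed outcomes.
- **That comparing baselines would be a far more powerful carryover test.** That holds only if the carryover is still present before the visit-2 exposure, and an equal shift in the response would then cancel in a change score.

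**Conclusion.** The carryover point holds without any numerical assumption: as described, sequence and period effects cannot identify carryover in a two-sequence, two-visit crossover, and a null result does not support adequate washout. The documents do not show that carryover is present or likely.

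The precision point holds if the change is taken from the visit baseline. The variance is then about 1.18 to 1.54 times that of a baseline-adjusted analysis for an assumed b of 0.7 to 0.3, with equal variances and ignoring the small cost of estimating one slope. A reader might infer that the trial is underpowered or its treatment estimate invalid. Neither follows: on the article's inputs HRV power stays far above 90%, and without carryover both analyses estimate the same randomised contrast without bias. Against a model that ignores the baseline, a change score can gain or lose, depending on the correlations. For blood pressure the consequence cannot be judged. The change is worth making, but the trial does not depend on it.

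**What to change.** 1. State the reference point of the change. Model the exposure-period value with the same-visit pre-exposure baseline as covariate, split into the participant's mean and the visit's deviation from it.
2. Keep treatment, period and sequence in every primary model, and stop describing the sequence and period terms as an evaluation of carryover.
3. Rest the washout argument on the separate-day design. Describe the visit-2 minus visit-1 pre-exposure baseline difference by sequence, with a confidence interval, and do not choose the model on it.

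The cost is one extra covariate (two terms once split) and one descriptive table. The article describes baseline biomonitor data at every visit, so no new measurement is needed. Two limits should be stated with it: the baseline check sees only carryover still present before the second exposure, and adjustment leaves the small residual bias noted above if baseline and response were shifted equally.

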#### 2.9.3. Correlation Structure

A covariance structure will be incorporated to account for within-subject correlation across repeated measures during each study day. Changes in health endpoints will be expressed as percent change with 95% confidence intervals.

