To address these gaps, we initiated the Green Oasis (GRO) project, designed to evaluate the environmental and health effects of dense urban plantings such as microforests, groves, or woodlets. Primarily, we will evaluate whether dense urban microforest installation modifies heat exposure and acute cardiovascular stress responses. Using a randomized crossover design, we assess the acute cardiovascular effects of walking in an urban setting before and after the installation of a compact, multilayered microforest. We hypothesize that clustered plantings will attenuate urban heat and reduce cardiovascular stress during exposure. Findings from this study are expected to provide novel insights into how small-scale, high-density greening interventions can improve cardiovascular resilience, helping to foster wellbeing in urban populations.

The primary objective of the Green Oasis (GRO) Project is to determine whether, in comparison with exposure to an impervious parking lot, exposure to an urban microforest improves cardiovascular and stress responses (heart rate variability and blood pressure). The secondary objective is to evaluate how exposure to the microforest affects stress biomarkers (catecholamines and cortisol), rumination, anxiety, and exposure to anthropogenic volatile organic compounds (VOC). Our exploratory analyses are to evaluate the effects of the microforest on surrounding environmental conditions (temperature, humidity, particulate matter, NO_2_, black carbon, and noise) and enhance ecological services (avian density, microbiome, etc). Lastly, the integrated objective is to integrate meteorological, ecological, and clinical data to evaluate whether environmental modifications mediate physiological responses. A summary of all research objectives/aims is listed in Table 1.

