#### 2.9.4. Secondary Analyses

Direct associations of temperature, humidity, and pollutants with health endpoints during walking will be evaluated using additional mixed-effects models. Exposure metrics will be averaged over defined time intervals, and endpoint changes will be estimated as percent differences.

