**Figure 6 ijerph-23-00365-f006:**
[figure not shown]

[figure not shown]
Schematic of the microforest planting design. Panels depict a high-density, multilayered planting arrangement of (**A**) trees and (**B**) shrubs modeled after natural forest succession.

**Table 1 ijerph-23-00365-t001:** Summary table outlining research aims, hypotheses, and outcome measures.

Aim	Hypothesis	Exposure	Outcome Measures
Primary Aim 1	Exposure to microforest improves HRV and lowers BP vs. parking lot	Microforest vs. impervious site	heart rate variability (HRV) and blood pressure (BP)
Secondary Aim 2	Exposure to microforest improves stress responses and decreases VOC exposure	Microforest vs. impervious surface	Salivary cortisol, urinary catecholamines and their metaboiltes, urinary VOC metabolites, self-reported stress and rumination.
Exploratory Aim 3	Microforest reduces heat and pollution	Pre/post intervention; spatial monitoring, comparison with adjacent impervious surface.	Temperature, humidity, PM, NO_2_, BC
Exploratory Aim 4	Microforest enhances ecological function	Pre/post intervention	Avian diversity, microbiome composition, GHG flux, ecosystem services
Integrated Aim 5	Environmental modification mediates physiological benefits	Integrated environmental metrics	HRV, BP with environmental covariates

**Table 2 ijerph-23-00365-t002:** Meteorological variables recorded by Tempest and Campbell Scientific stations (temperature is measured with passively aspirated sensors in the Tempest stations and with fan-aspirated sensors in the Campbell Scientific station).

Variable	Tempest Stations	Research Station
Temperature (°C)	Passively Aspirated	Fan-Aspirated
Relative Humidity (%)	Passively Aspirated	Fan-Aspirated
Barometric Pressure (hPa)	√	√
Wind speed (m s^−1^)	√	√
Wind Direction (°)	√	√
Dewpoint Temperature (°C)	Calculated	Calculated
Solar Radiation (W m^−2^)	√	√

**Table 3 ijerph-23-00365-t003:** Demographic characteristics of study participants in Wave 1 (2023) and Wave 2 (2024).

	Wave 1 (2023)	Wave 2 (2024)
Age	39 [28 to 42]	42 [29 to 52]
Sex		
Male	16 (40%)	20 (40%)
Female	24 (60%)	30 (60%)
Race		
NHW	30 (75%)	28 (56%)
NHB	3 (8%)	10 (20%)
HW	0 (0%)	3 (6%)
HB	0 (0%)	0 (0%)
Other	7 (17%)	9 (18%)
Education		
≤4-year degree	21 (53%)	27 (56%)
>4-year degree	19 (47%)	22 (44%)
Income		
<$90 K	19 (47%)	27 (54%)
>$90 K	18 (45%)	21 (42%)
Declined/Don’t know	3 (8%)	2 (4%)

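### Percent change is fixed as the effect scale for all health endpoints; it does not suit the questionnaire scores, and its calculation is left open for the others

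*Protocol article*

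**What the plan says.** - **Effect scale.** Section 2.9.3 states: "Changes in health endpoints will be expressed as percent change with 95% confidence intervals". Section 2.9.4 says of the secondary models that "endpoint changes will be estimated as percent differences". Neither sentence names an exception, and the article does not define which measures count as health endpoints.
- **Primary outcomes and model.** Section 2.9.2: "The primary outcomes are changes in HRV and blood pressure". It continues: "Linear mixed-effects models will be used to evaluate associations between temperature and these outcomes", with participant as random effect and with treatment and sequence as fixed effects.
- **Transformation.** Section 2.9.1 adds only that "skewed outcomes will be transformed as appropriate"; the log is not named.
- **Questionnaires.** The secondary objective in the Introduction includes rumination and anxiety. The Aim 2 row of Table 1 ends with "urinary VOC metabolites, self-reported stress and rumination". Section 2.6.3 names the instruments: the STAI for anxiety, the BSRI for rumination (from 2025), and, for 2024, "the Subjective Units of Distress Scale (SUDS) was added to measure distress". No score ranges are given.
- **Axillary temperature.** It is measured from Wave 2 (Section 2.6.4, Table 4) but is not listed as an outcome of any aim.

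**The concern.** A percentage has a fixed meaning only for a quantity with a true zero. SDNN, blood pressure and concentrations have one. A questionnaire total does not: its minimum is a scoring convention. Temperature in Celsius or Fahrenheit does not either. Applied as written, the rule would report named secondary outcomes on a scale where the size of the effect reflects the scoring convention as much as the participants' answers. Anyone starting at zero would have no value, and anyone starting near zero would carry great weight.

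For the positive endpoints the question is how the percentage is obtained. Sections 2.9.2 and 2.9.3, read together, could be taken to mean that each person's change is divided by that person's baseline and then averaged. The text does not say this, but it does not exclude it. That average has a positive expectation even when nothing changes.

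**Working it through.** The plan states no figure on the percent scale, so there is nothing to reproduce. The check has three parts.

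**1. Questionnaire scores: dependence on origin.** Illustration, with the scale minimum and the scores assumed:
- Scale with minimum 20, from 30 to 26: -4/30 = -13.3%.
- Same answers rescored from 0, from 10 to 6: -4/10 = -40%.
- Difference in points: -4 in both cases.

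With a baseline of 0 the ratio has no value. Assume that the scale minimum is 0 and that a share z of participants, 10 to 30%, scores 0 at a visit's baseline. Under a per-person ratio, the share of crossover pairs lost is z (10 to 30%) if the same people score 0 at both visits, and 1 - (1 - z)² if zeros are independent: 1 - 0.9² = 19% to 1 - 0.7² = 51%. A log model does not remove the difficulty, because log(0) does not exist either.

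**2. Axillary temperature: dependence on unit.** A rise of 0.5 °C from an assumed 36.0 °C:
- Celsius: 0.5/36.0 = 1.39%.
- Fahrenheit: 0.9/96.8 = 0.93%.

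**3. Positive endpoints: per-person percentages against model-based ones.** Let baseline and post values be lognormal with the same distribution, coefficient of variation CV and log-scale correlation ρ, with no true change. Then

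E[post/base] - 1 = (1 + CV²)^(1-ρ) - 1.

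SDNN, with means and SD from Section 2.10 and ρ assumed:
- Mean 22.6, SD 6.7: CV = 0.296, 1 + CV² = 1.0879. At ρ = 0.3: 1.0879^0.7 - 1 = +6.1%. At ρ = 0.5: 1.0879^0.5 - 1 = +4.3%.
- Mean 31.0, SD 6.7: CV = 0.216, 1 + CV² = 1.0467. At ρ = 0.7: 1.0467^0.3 - 1 = +1.4%.

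A simulation with normal instead of lognormal values (mean 22.6, SD 6.7, values of 3 or below excluded) gave +12%, +6% and +2.5% at ρ = 0, 0.5 and 0.8.

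Biomarkers, with CV and ρ assumed:
- CV 0.5, ρ = 0.7: 1.25^0.3 - 1 = +7%.
- CV 1.0, ρ = 0.5: 2^0.5 - 1 = +41%.

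In 400,000 simulated pairs with uncorrelated errors and no true change:

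| CV | Mean of per-person percent changes | Back-transformed log difference |
|---|---|---|
| 10% | +1.0% | -0.02% |
| 20% | +4.0% | +0.03% |
| 30% | +9.0% | -0.06% |
| 50% | +25.0% | +0.02% |
| 80% | +64.1% | +0.03% |

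The last column is zero within simulation error.

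**Effect on the planned comparison.** Both sites carry the same drift. At CV 50% with uncorrelated errors, the contrast with no effect is 1.25 - 1.25 = 0 (simulated: -0.2 points). With a true 10% reduction at one site it is 0.9 × 1.25 - 1.25 = -12.5 points (simulated: -12.7). So the per-person calculation stretches a real contrast but does not create one.

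**The case against.** The strongest reply is that the per-person ratio appears nowhere in the article. The plan speaks of linear mixed models, repeated measures within each study day and transformation of skewed outcomes. A log-scale model of the measured values, back-transformed to a percentage, fits all of that and carries no drift. The effect scale for each endpoint is also a detail that a condensed article may leave to the full analysis plan. Most of this stands, and it rules out several stronger readings that a reader might infer:

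- **That HRV and biomarker changes will be overstated.** This holds only under the per-person calculation, which the article does not specify.
- **That a log model is impossible because a change can be negative.** This is too literal. The repeated measured values can be modelled on the log scale and the change taken as a contrast.
- **That type I error is inflated.** Under the per-person calculation, a one-sample test of within-site SDNN change at nominal 2.5% and n = 50 rejects in simulation about 4 to 10% of the time. No such test is planned; Section 2.9.2 tests treatment and its interaction with temperature.
- **That power for the site contrast falls.** The simulated losses, for instance from 79% to about 72% at CV 0.7, again need the per-person calculation, and also an assumed CV, correlation and 30% effect.
- **That participants without distress will drop out.** The article gives neither score ranges nor the frequency of zeros.

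Two further limits apply. Axillary temperature is an outcome of no aim, so its coverage is an inference. Section 2.9.4 concerns endpoints during walking and hardly reaches questionnaires completed indoors.

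The reply does not remove the questionnaire point. Section 2.9.3 states a rule rather than leaving one out, and an analysis plan that followed it would inherit the problem for outcomes that the article itself names.

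**Conclusion.** The point holds in a limited form and is minor. As worded, the rule gives origin-dependent figures for the anxiety, distress and rumination scores; that needs no assumption beyond the scores being health endpoints, which their place in the secondary objective and Aim 2 supports. Values undefined at baseline arise only if a scale can score zero. The temperature example matters only if axillary temperature is analysed.

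For SDNN, blood pressure, cortisol and urinary metabolites percent change is a legitimate scale. What is left is an ambiguity: one possible calculation drifts upward within a site, by +1.4 to +6.1% for SDNN at correlations of 0.3 to 0.7 under the lognormal model and by more for noisier markers. The drift cancels between sites when there is no effect. The primary comparison of microforest with parking lot is not invalidated.

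**What to change.** Reword the sentence in Section 2.9.3 along these lines:

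- For positive ratio-scale endpoints, obtain percent change from a mixed model of the log of the measured values, reported as a ratio of geometric means (as a percent difference) with 95% confidence interval. State that per-person percentages of baseline are not averaged.
- For STAI, SUDS and BSRI scores, and for axillary temperature if it is analysed, report mean differences in original units with 95% confidence interval.

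Section 2.9.4 can refer to the same rule. Whether blood pressure is reported in mmHg or in percent is a matter of preference and need not change.

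The cost is wording only, plus the loss of one common percent scale across endpoints. No design or data collection changes, and with Waves 4 and 5 planned for 2026 and 2027 the rule can be settled before the final analysis.
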